### Sample size and power

Sample size was estimated to determine the superiority of the prophylactic naloxone infusion compared to placebo in reducing the rate of respiratory depression. Based on an audit of 29 patient charts in our unit containing information on respiratory depression, the percentage of the target patient population who develop respiratory depression without treatment is estimated to be 31% (95% confidence interval (CI) 14.2–47.9%). This is based on the definition of respiratory depression in the ASA guidelines for prevention of respiratory depression with ITM [40].

A clinically significant difference was defined as a 75% reduction in the percentage of respiratory depression among those on treatment, compared to those on placebo. Given the estimate of 31% for the placebo group, this is equivalent to a clinically significant relative risk of 4 (a four-times greater risk of respiratory depression for patients on placebo, than for those on treatment).

Sample size calculations are based on a superiority hypothesis test of the risk of respiratory depression, formulated with the objective of testing whether the risk of respiratory depression is less for those on treatment than for those on placebo. To achieve a power of 80% for this test at a 5% significance level, a sample size of 43 per group is required or a total sample size of 86. This sample size calculation was calculated based on a one-tailed, two-proportion Z test with continuity correction.

After commencement of the study the sample size was inflated to compensate for an un-anticipated dropout rate of up to 10%. The final sample size is 96 (48 per treatment group).

### Primary outcome analysis

The primary outcome will be summarised as the number and percentage of patients in each treatment arm who develop respiratory depression within the study period. Percentages will be calculated using the number of patients for whom data are available as the denominator. Denominators will also be reported.

Risk of respiratory depression will be compared across treatment arms using a risk ratio with an associated 95% CI.

The primary analysis will test the superiority hypothesis that the risk of respiratory depression is reduced for patients receiving a prophylactic naloxone infusion, compared to patients receiving a placebo infusion. The primary outcome will be modelled as a binomial random variable, using a one-sided, two-proportion Z test, with continuity correction.

Sensitivity analysis of the primary outcome will be conducted using logistic regression modelling, adjusting for potentially relevant covariates, to determine whether the estimated treatment effect differs after covariate adjustment. Potentially relevant covariates to be considered include:AgeBMI (Body Mass Index), Duration of surgeryDuration of study infusionTime from injection of ITM to end of studyDose of intraoperative intravenously administered fentanylDose of postoperative intravenously administered fentanyl

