Binary secondary outcomes include: presence of absence of pruritus, presence or absence of nausea, and/or presence or absence of vomiting, any Ramsey Sedation Score ≥ 3 and any PaCO_2_ > 6.66 kPa. Each binary secondary outcome will be summarised by treatment group, using frequencies and percentages. Ratios of relative risk will be presented with 95% CIs, for comparison of naloxone and placebo groups. Odds ratios with 95% CIs will also be calculated and presented in supplementary material. For each binary secondary outcome, a two-sided Z test will test the hypothesis of a difference in the outcome between naloxone and placebo. Sensitivity analyses will be conducted for binary secondary outcomes with logistic regression models, adjusting for relevant covariates (as listed above for the primary outcome) to determine whether the estimated treatment effect differs after adjustment for these covariates.

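### With about 17 to 19 expected events, an ordinary logistic model with all seven listed covariates would by itself push a true treatment effect further from the null, so a change after adjustment could not be read as a covariate effect

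*Protocol article*

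**What the plan says.** The primary analysis is a one-sided two-proportion Z test with continuity correction, with a risk ratio and 95% CI as the effect measure (Primary outcome analysis). The same section adds: "Sensitivity analysis of the primary outcome will be conducted using logistic regression modelling, adjusting for potentially relevant covariates". The purpose given is "to determine whether the estimated treatment effect differs after covariate adjustment".

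Seven covariates are listed for consideration: age, BMI, duration of surgery, duration of study infusion, time from intrathecal morphine to end of study, intraoperative fentanyl dose and postoperative fentanyl dose. The article names no selection rule, no limit on their number and no penalised or exact fitting method. The list is used again under Secondary outcome analysis: "Sensitivity analyses will be conducted for binary secondary outcomes with logistic regression models, adjusting for relevant covariates (as listed above for the primary outcome").

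The expected number of events follows from Sample size and power. There, "the percentage of the target patient population who develop respiratory depression without treatment is estimated to be 31"% ("95% confidence interval (CI) 14.2–47.9"%, from 29 charts), and "A clinically significant difference was defined as a 75% reduction in the percentage of respiratory depression among those on treatment". The target is 43 per group, raised to 48 per group for dropout of up to 10%.

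**The concern.** The outcome is one yes/no result per patient, so the number of events is the number of patients with any episode. Maximum-likelihood logistic regression is biased away from the null when events are few relative to coefficients, and the bias grows with each added term, whether or not the covariate matters.

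The purpose of this analysis is to see whether the effect moves when covariates are added. Fitting artefact and genuine covariate effect show up in the same place, as a gap between two estimates from the same patients. If naloxone works, the artefact favours naloxone. A reader could then take the adjusted result as evidence that the effect holds or strengthens once covariates are accounted for, when the covariates contributed nothing.

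**Working it through.** **1. Reproduce the plan's sample size.** Inputs: placebo rate 0.31; naloxone rate 0.25 × 0.31 = 0.0775; difference 0.2325; one-sided 5%; power 80%.

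- Uncorrected: n = [1.645 × √(2 × 0.19375 × 0.80625) + 0.842 × √(0.31 × 0.69 + 0.0775 × 0.9225)]² / 0.2325² ≈ 34.7.
- Continuity-corrected: (34.7/4) × [1 + √(1 + 4/(34.7 × 0.2325))]² ≈ 42.8, so 43 per group and 86 in all, as stated.
- Dropout: 86/0.90 = 95.6, so 96, as stated.

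The sizing is not in error, so its rates can be used for the event count.

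**2. Expected events.**

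- 48 per group: 48 × 0.31 = 14.9 and 48 × 0.0775 = 3.7; total 18.6.
- 43 per group (after the allowed dropout): 13.3 + 3.3 = 16.7.

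**3. Events per coefficient (excluding the intercept).**

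- Treatment plus seven covariates: 18.6/8 = 2.3, or 16.7/8 = 2.1.
- Treatment plus five: 18.6/6 = 3.1.
- Over the audit interval (14.2% to 47.9%, same 75% reduction, 96 patients): 8.5 to 28.7 events, or 1.1 to 3.6 per coefficient with seven covariates.

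**4. What the model does.** Odds ratios are placebo to naloxone. True value: (0.31/0.69)/(0.0775/0.9225) = 5.35, log 1.677. Several thousand trials per setting were simulated with 48 per group and independent standard-normal covariates of no effect, fitted by maximum likelihood. Trials with no finite estimate (about 2%) were left out.

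| Covariates | Mean log OR | Geometric-mean OR | Adjusted OR more than 20% above unadjusted |
|---|---|---|---|
| 0 | 1.76 | 5.8 | – |
| 2 | 1.80 | 6.0 | about 9% of trials |
| 5 | 1.87 | 6.5 | about 29% |
| 7 | 1.94 | 7.0 | about 43% |

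With seven covariates:

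- The adjusted OR is the larger in about 80% of trials.
- The mean adjusted log OR is 1.93 to 1.95, and 1.93/1.677 = 1.15, about 15% too far from the null. The unadjusted fit is itself about 4% too far (1.75/1.677), so not all of the excess comes from the covariates.
- The shift caused by adding covariates is about 0.19, against a median standard error of 0.70: 0.19/0.70 = 0.27 of a standard error.
- At 43 per group the mean shift is about 0.22, and the adjusted OR is more than 20% larger in about 48% of trials.
- Covariates correlated at 0.9 give the same picture (mean shift 0.18).

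**5. What is not affected.** In the same seven-covariate model, 95% CI coverage is about 97% at the planned rates. With no treatment effect (about 30 events) the mean log OR is within 0.01 of zero and one-sided type I error is 5.8%.

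**6. If the covariates do matter.** With a log OR of 0.3 per SD for each, the conditional true log OR is 1.82 and the adjusted mean is 2.16, 19% too far (2.16/1.82). A further part of the gap from the unadjusted estimate, 1.82 − 1.68 = 0.14, is non-collapsibility of the odds ratio. That is neither bias nor confounding.

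**7. With Firth's penalty on both models.** The mean shift with seven covariates is about 0.00 (SD about 0.20). The adjusted OR exceeds the unadjusted by more than 20% in about 14% of trials with seven covariates and about 5% with two.

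**The case against.** **The eight-term model is not fixed.** The seven are offered as candidates, and a selection rule may sit in an analysis plan that is not shown. This stands, so the point is conditional on all or most of them entering. Two things limit it. The secondary analysis section points back to the list as its adjustment set, and five covariates still give a spurious rise above 20% in about 29% of trials.

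**A blind review precedes the final analysis.** The Blinding section provides for a review of whether the planned analysis is suitable, and the pooled event count would be visible then. This mitigates the problem, but the text does not mention the number of covariates or the fitting method.

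**The adjusted analysis still works as inference.** A reader might infer that it cannot serve as a sensitivity check at all. The documents' figures do not support that: coverage is near nominal, there is no bias under no effect, and the shift is small against the standard error of one trial. The inflation enlarges a real effect and does not create one. What remains is that the stated use compares two estimates from the same patients, and there the shift is systematic.

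**Risk ratio against odds ratio.** At planned rates the risk ratio is 4.0 and the odds ratio 5.35, and a reader might infer that the plan will set one against the other. It does not say so; an unadjusted odds ratio is the natural comparator. The fix need only make the common scale explicit.

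**Non-finite estimates.** At 48 per group the chance of no naloxone events is 0.9225^48 = 2.1%. The placebo-to-naloxone risk ratio is then not finite either, so this is not a defect particular to the adjusted model.

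**Conclusion.** The point holds as a conditional and moderate one. If the seven listed covariates enter an ordinary logistic model at the plan's own rates, about 2 events per coefficient push a true effect about 15% too far from the null on the log-odds scale. Adding the covariates accounts for a shift of roughly a quarter of a standard error. A strengthening after adjustment is then the expected result even with irrelevant covariates, so it cannot be read as a covariate effect. The sample size, the primary Z test and the primary risk ratio are unaffected.

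This rests on the planned 31% and 75% reduction, unpenalised fitting, and normal covariates independent of treatment. Across the audit interval for the placebo rate the mean shift stays near 0.2 (0.23 at 14.2%, 0.21 at 47.9%).

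A reader might also infer that every binary secondary outcome has the same problem. The article gives no event rates for pruritus, nausea, vomiting, sedation or raised PaCO2, and its Background describes the risks of pruritus and of nausea and vomiting as considerable. Their counts could be much higher, so the argument carries over only where the observed count proves similarly low.

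**What to change.** In Primary outcome analysis, state that both the unadjusted and the adjusted sensitivity models will be fitted by Firth-penalised logistic regression, and that they will be compared on one scale: odds ratio with odds ratio, or both as marginal risk ratios. Penalising both removes the systematic shift.

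Preferably, also name in advance a small set of baseline covariates from the existing list, for example age and BMI. Penalisation alone removes the mean shift; the smaller set limits chance movement between the two estimates. Under Secondary outcome analysis, apply the same method to any binary outcome whose event count turns out similarly low.

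The cost is a few sentences, standard software and slightly more analysis work. If the set is reduced, fewer of the listed covariates are examined.

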### Secondary outcome analysis

Maximum pain score in 24 h will be calculated for each patient. Descriptive statistics for maximum pain score will be calculated and compared across treatment groups. A Mann-Whitney *U* test will test the hypothesis of a difference in the distribution of maximum pain scores between naloxone and placebo.

Line charts will be used to display hourly pain scores over a 24-h period, by treatment group, and to identify differences in patterns of pain over time between treatment groups. Pain scores over time will be modelled using a generalised mixed-effects model, with an appropriate link function, in order to test for differences in patterns of pain over time for naloxone and placebo. This model will be adjusted for relevant covariates (as for the primary outcome) to determine sensitivity of pain score patterns to these covariates.

Requirement for supplemental fentanyl (mcg) will be summarised by treatment group with appropriate summary statistics. A *t* test, or equivalent non-parametric alternative where appropriate, will test the hypothesis of a difference in the mean requirement for supplemental fentanyl between naloxone and placebo. Sensitivity analysis will be conducted using linear regression modelling, adjusting for relevant covariates (as for the primary outcome), to determine whether the estimated treatment effect differs after covariate adjustment.

Scores on patient satisfaction with mode of analgesia by treatment group. A Mann-Whitney *U* test will test the hypothesis of a difference in the distribution of scores of patient satisfaction with analgesia between naloxone and placebo.

Binary secondary outcomes include: presence of absence of pruritus, presence or absence of nausea, and/or presence or absence of vomiting, any Ramsey Sedation Score ≥ 3 and any PaCO_2_ > 6.66 kPa. Each binary secondary outcome will be summarised by treatment group, using frequencies and percentages. Ratios of relative risk will be presented with 95% CIs, for comparison of naloxone and placebo groups. Odds ratios with 95% CIs will also be calculated and presented in supplementary material. For each binary secondary outcome, a two-sided Z test will test the hypothesis of a difference in the outcome between naloxone and placebo. Sensitivity analyses will be conducted for binary secondary outcomes with logistic regression models, adjusting for relevant covariates (as listed above for the primary outcome) to determine whether the estimated treatment effect differs after adjustment for these covariates.

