## Discussion

Intrathecally administered morphine is an effective component of multimodal analgesia for hepatopancreaticobiliary surgical patients. However, the risk of respiratory depression necessitates a higher monitoring workload than would otherwise be necessary. The administration of a prophylactic naloxone infusion has the potential to reduce this risk, making ITM a potentially viable and safer option for patients (Additional file 1).

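### Pain scores are analysed by hypothesis tests with no stated between-arm difference or confidence interval, so the plan as written gives little basis for judging whether analgesia is preserved under naloxone

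*Protocol article*

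**What the plan says.** All of the following is from the protocol article.

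- **Maximum pain** (Secondary outcome analysis): "Descriptive statistics for maximum pain score will be calculated and compared across treatment groups". The inferential step is a rank test (Mann-Whitney), described as follows: "test will test the hypothesis of a difference in the distribution of maximum pain scores between naloxone and placebo".
- **Hourly pain** (same section): line charts by arm, and a generalised mixed-effects model "in order to test for differences in patterns of pain over time for naloxone and placebo". On covariates: "This model will be adjusted for relevant covariates (as for the primary outcome) to determine sensitivity of pain score patterns to these covariates". The primary-outcome list of covariates to be considered includes the postoperative fentanyl dose.
- **Rescue fentanyl** (same section): a t test or non-parametric alternative "will test the hypothesis of a difference in the mean requirement for supplemental fentanyl between naloxone and placebo", then linear regression "to determine whether the estimated treatment effect differs after covariate adjustment".
- **Satisfaction with analgesia** (same section): a Mann-Whitney U test.
- **By contrast**, the primary outcome gets a risk ratio with a 95% CI (Primary outcome analysis). For the binary secondary outcomes: "Ratios of relative risk will be presented with 95% CIs, for comparison of naloxone and placebo groups".
- **Decision rule** (Statistical analysis plan): significance at p below 0.05 for primary and secondary outcomes.
- **Sample size** (Sample size and power): set on respiratory depression only. No SD, margin or power is given for pain.
- **Discussion**: the infusion may lower the risk of respiratory depression, "making ITM a potentially viable and safer option for patients".

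**The concern.** Naloxone is an opioid antagonist given to patients who depend on intrathecal morphine for pain relief, so any reader of the results will ask whether the pain relief survives. The plan fixes intervals for the benefit and for side effects such as pruritus and nausea. For pain scores it fixes tests of a difference.

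A test of a difference in a trial not sized for that outcome answers the question poorly. A significant result shows a loss but, without an estimate, not how large it is. A non-significant result leaves open both no loss and a relevant loss.

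Two features add to this:

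- If differences in pattern are taken to mean a treatment-by-time interaction only, the model's test would not respond to pain that is higher by the same amount at every hour.
- Rescue fentanyl is a response to pain after randomisation. Adjusting the pain model for it could hide lost analgesia, because patients in more pain receive more fentanyl, which lowers their scores.

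**Working it through.** **1. The plan's own sample size.** Inputs from Sample size and power: 31% on placebo, a 75% reduction (so 0.31 × 0.25 = 7.75% on naloxone), one-sided 5%, 80% power, continuity correction. The mean proportion is 0.19375.

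- Uncorrected: n = [1.645 × √(2 × 0.19375 × 0.80625) + 0.842 × √(0.31 × 0.69 + 0.0775 × 0.9225)]² / 0.2325² = 34.7.
- Corrected: (34.7/4) × [1 + √(1 + 4/(34.7 × 0.2325))]² = 42.8, so 43 per group and 86 in total.
- Dropout: 86/0.9 = 95.6, so 96.

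All three stated figures reproduce. None of them concerns pain.

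**2. What a test on maximum pain can miss.** The documents give no SD for pain, so a range is assumed, with a true rise of 1 point on the 0–10 scale. With 48 per arm, SE = SD × √(2/48). Normal-approximation power is Φ(1/SE − 1.96). The 95% CI half-width is 1.986 × SE.

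| Assumed SD of maximum pain | SE | CI half-width | Missed, normal approximation | Missed, simulated Mann-Whitney |
|---|---|---|---|---|
| 1.5 | 0.306 | 0.61 | 10% | not run |
| 2 | 0.408 | 0.81 | 31% | 35% |
| 2.5 | 0.510 | 1.01 | 50% | 53% |
| 3 | 0.612 | 1.22 | 63% | 66% |

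The simulation used 4,000 trials with scores rounded and cut to 0–10. The cutting shrinks the realised mean shift to 0.99, 0.95 and 0.89 points at SD 2, 2.5 and 3, which accounts for part of the higher miss rates. The range 31% to 66% spans both columns for SD 2 to 3. With 43 per arm, the half-widths are 0.64, 0.86, 1.07 and 1.29.

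**3. What the planned hourly data could deliver.** Assumptions: 16 hourly scores per patient, hourly SD 2 (a different quantity from the SD of the maximum in step 2), first-order autocorrelation 0.5 within patient, and an intraclass correlation (ICC) of 0.3 to 0.7. The variance of a patient's mean score is 4 × [ICC + (1 − ICC) × 0.172], where 0.172 = [1 + 2 Σ(1 − k/16) × 0.5^k]/16, summed over k = 1 to 15.

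- ICC 0.3: variance 1.68, SE 0.265, half-width 0.53, power for a uniform 1-point rise 97%.
- ICC 0.5: variance 2.34, SE 0.313, half-width 0.62, power 89%.
- ICC 0.7: variance 3.01, SE 0.354, half-width 0.70, power 81%.

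Simulation on the bounded scale agrees: half-width about 0.5 to 0.7 points and power 80% to 96%. In the same simulation the Mann-Whitney test on the maximum detected the rise in 73% to 87% of trials. So under these assumptions the data can bound average pain to within about 0.7 points, but the stated plan does not ask for that interval.

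**4. The pattern test.** A uniform rise has no treatment-by-time interaction apart from the limits of the scale. A test of interaction alone therefore rejects at about its 5% level. This follows from that reading of the model and is not an independent result.

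**The case against.** The strongest reply has four parts.

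- **Detail left to a fuller document.** Which contrast a mixed model reports, and whether a rank test carries an interval, can be left to an analysis plan that is not shown. The model will in any case yield estimates with standard errors. This has weight and lowers the severity. It does not dispose of the point, because the article does fix intervals for the primary and binary outcomes and, for pain, fixes tests.
- **Analgesia is not judged by two tests alone.** A reader might infer that it is. The documents do not support this: rescue fentanyl and satisfaction are also analysed, by-arm summaries and charts of pain are planned, and the fentanyl regression gives an estimated effect. What stands is that none of these has a stated interval or a reference difference.
- **No claim of preserved analgesia is made.** A reader might infer that the trial intends to take p > 0.05 as proof that analgesia survives. No section says so or sets a non-inferiority aim for pain, and the Discussion sentence is hedged and concerns respiratory depression. The point is a limit on interpretation and not a contradiction.
- **The pattern test is not necessarily blind to a uniform rise.** The protocol specifies neither an interaction nor linear time, and a model comparison that includes the treatment term would detect such a rise. The 5% figure therefore holds only on the narrow reading.

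It is also fair that the maximum-score test is not much weaker than the time average under the step 3 assumptions (73% to 87% against 80% to 96%). The case for the time average rests mainly on its giving an interpretable difference with an interval.

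**Conclusion.** The point holds as a weakness in the stated method, of minor to moderate severity. Both pain-score analyses are framed as tests without a between-arm estimate or interval, the other analgesia measures have no stated interval either, and the sample size gives no assurance about pain. If the pain tests are non-significant, the plan as written gives no other basis for saying how much analgesia might have been lost.

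The size depends on assumptions. A 1-point rise in maximum pain would be missed in roughly 31% to 66% of trials at 48 per arm if the SD is 2 to 3, but in only about 10% if it is 1.5. The 1-point rise is itself illustrative, since the documents define no relevant pain difference. The primary analysis is unaffected.

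**What to change.** 1. From the mixed model already planned, report the time-averaged naloxone minus placebo difference in hourly pain with its 95% CI as the main pain result. Do not adjust that estimate for postoperative fentanyl dose. Keep the pattern test as secondary, and state which model terms it tests.
2. Add a Hodges-Lehmann difference with 95% CI to the maximum-score test.
3. Report a between-arm difference with 95% CI for rescue fentanyl. Pain scores alone could mislead, because equal scores reached with more rescue are not equal analgesia.
4. State that any conclusion about preserved analgesia will come from these intervals read together, against pain and fentanyl differences that the investigators set before unblinding, and not from p > 0.05.

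The cost is a few sentences and some extra output from analyses already planned, with no new data or patients. The downside is that the intervals may be too wide to support a statement that analgesia is preserved. In that case the report should say so.

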### Outcome measures

The primary outcome of this trial is the rate of respiratory depression during the study period for patients receiving naloxone infusion compared to placebo. Respiratory depression will be diagnosed based mainly on criteria derived from the American Society of Anesthesiologist’s (ASA) ‘Practice Guidelines for the Prevention, Detection and Management of Respiratory Depression Associated with Neuraxial Opioid Administration’ [40] 2016 document. The criteria we will use are: respiratory rate < 10 and/or a decrease in SpO_2_ to < 92% and/or an increase in FiO_2_ required to maintain SpO_2_ > 92%. The primary outcome will be recorded as a dichotomous variable, recording any episode of respiratory depression during administration of the study infusion. Study infusion will be administered from within 60 min of extubation until 8:00 a.m. on the first postoperative morning.

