### Secondary outcomes

Secondary outcomes will be recorded as the occurrence of the dichotomous variables presence or absence of pruritus and nausea/vomiting at any time over the monitoring period, and continuous outcomes will be assessed over the same time period.Incidence of pruritusPresence or absence of pruritus will be recorded on an hourly basis, along with the need for any rescue medication for treatment of pruritus
Incidence of nausea and vomitingPatients will be asked to report any incidence of nausea on an hourly basis and any episode of vomiting will be recorded. The use of any antiemetic agents, the frequency of administration and the total dose required will be recorded
Ramsey Sedation ScoreThe Ramsey Sedation Score will be recorded on an hourly basis. Any change in sedation score in the treatment arm will be assessed
Pain scoresWe use a numerical rating scale from 0 to 10 in assessing pain in our unit, and this will be recorded on an hourly basis
Requirement for supplemental fentanyl (rescue analgesia)Total dose of rescue intravenously administered fentanyl administered during the study period will be assessed
Patient overall satisfaction with analgesiaWe will utilise a simple Visual Analogue Scale, which will be scored at the end of the study period, by the investigator
Rate of respiratory depression associated with a Ramsey Sedation Score ≥ 3We will assess the respiratory depression parameters listed above, combined with Ramsey Sedation Scores
Rate of respiratory depression associated with a PaCO_2_ ≥ 50 mmHgWe will assess the respiratory depression parameters, combined with the 2-hourly PaCO_2_ results
Any differences in haemodynamic parameters between study groupsWe will compare heart rate (HR), systolic and diastolic blood pressures and need for any vasopressor support between the two groups
Major adverse events, adverse events and protocol deviations will be recorded and compared between the two groups

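### The adjusted analysis of rescue fentanyl borrows a covariate list that contains postoperative fentanyl dose, so the outcome, or nearly the same quantity, can enter its own regression

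*Protocol article*

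**What the plan says.** Four statements in the protocol article bear on this.

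- **The outcome** (Secondary outcomes): "Total dose of rescue intravenously administered fentanyl administered during the study period will be assessed". For the timing, Outcome measures says: "Study infusion will be administered from within 60 min of extubation until 8:00 a.m. on the first postoperative morning". The dose is therefore accumulated wholly after the operation.
- **The main comparison** (Secondary outcome analysis): a t test, or a non-parametric equivalent, "will test the hypothesis of a difference in the mean requirement for supplemental fentanyl between naloxone and placebo". It has no covariates.
- **The adjusted comparison** (same section): "Sensitivity analysis will be conducted using linear regression modelling, adjusting for relevant covariates (as for the primary outcome"). Its stated purpose is "to determine whether the estimated treatment effect differs after covariate adjustment".
- **The covariates** (Primary outcome analysis): the list opens with "Potentially relevant covariates to be considered include" and names seven items: age, BMI, duration of surgery, duration of infusion, time from the intrathecal injection to the end of study, intraoperative IV fentanyl dose and postoperative IV fentanyl dose. The two fentanyl doses are separate items.

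This is the only covariate list in the article. Nothing removes the last item when postoperative fentanyl is the dependent variable.

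**The concern.** The list was drawn up for respiratory depression, where postoperative fentanyl dose is at least a different variable from the outcome. Carried over by cross-reference to the fentanyl model, it places postoperative fentanyl on both sides of the equation. The covariate then absorbs the variation that the treatment term is meant to explain.

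At stake is the interpretation of one sensitivity analysis. Its purpose is to compare the adjusted with the unadjusted effect. If naloxone changed rescue fentanyl use, the unadjusted comparison could show it while the adjusted model showed little or nothing, for a purely mechanical reason. A reader could take that as evidence that the difference was due to confounding. Rescue opioid use is one of the ways in which the trial would see a loss of analgesia under naloxone, so a spurious adjusted null would reassure wrongly.

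**Working it through.** **Figures in the plan.** The article gives no mean, SD or target difference for fentanyl, so there is no plan figure for this model to reproduce. The only related figure is the sample size, which sets the group size used below. The inputs are 31% on placebo, 31% × 0.25 = 7.75% on naloxone, a one-sided 5% level, 80% power and a continuity correction. They give 43 per group, and 86 / (1 − 0.10) = 95.6, rounded up to 96, or 48 per group. Both agree with the article, and neither depends on the point made here.

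**Step 1: identical variables.** Let Y be rescue fentanyl dose, T treatment, Z the other covariates and X postoperative fentanyl dose. The model is

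Y = a + bT + c′Z + dX + error.

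If X = Y, setting a = 0, b = 0, c = 0 and d = 1 gives a residual sum of squares of 0. No other fit can do better, and with a full-rank design this one is unique. The treatment coefficient is therefore 0 and R-squared is 1 for every dataset. No assumption about the distribution of doses is needed.

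**Step 2: nearly identical variables.** The two could differ, for example if X also counts fentanyl given between extubation and the start of the infusion. Write X = Y + U, with U independent of Y, T and Z and with SD s. Let Δ be the true treatment difference in Y, and σ the SD of Y given T and Z. Then

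- d = σ² / (σ² + s²)
- b = Δ − dΔ = Δ × s² / (σ² + s²)

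**Step 3: numbers.** The following are assumed and are not in the article: Δ = 60 mcg, σ = 100 mcg, and one further baseline covariate with a coefficient of 10 mcg per SD. With 48 per arm and 2,000 simulated trials for each row:

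| s (mcg) | Mean correlation of X and Y | b by formula (mcg) | Mean simulated b (mcg) | Share of Δ kept, by formula |
|---|---|---|---|---|
| 0 | 1.00 | 0 | 0.0 | 0% |
| 10 | 0.995 | 60 × 100 / 10,100 = 0.6 | 0.6 | 1% |
| 25 | 0.97 | 60 × 625 / 10,625 = 3.5 | 3.6 | 6% |
| 50 | 0.90 | 60 × 2,500 / 12,500 = 12.0 | 11.6 | 20% |
| 100 | 0.72 | 60 × 10,000 / 20,000 = 30.0 | 30.2 | 50% |

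In the first row, the largest absolute estimate over all 2,000 trials was about 2 × 10⁻¹³, which is rounding error. With X left out, the mean estimate was between 59.5 and 60.2 mcg in every row. The share kept depends only on s/σ, so choosing another Δ does not change the last column.

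**The case against.** The strongest defence is the wording. The list contains candidates to be considered, and the fentanyl model is to use relevant ones. A statistician could fairly say that an outcome is never a relevant covariate for itself and leave it out without breaking the plan. A perfect fit would also expose the error at once. The blind review described under Blinding, which is to decide before final analysis whether the planned analyses are appropriate, is a further chance to catch it.

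Much of this stands. A reader might infer that the adjusted model must report no effect whatever the data show. The documents do not support that: it follows only if the candidate is used and the two variables coincide. The defence does not remove the fault, however. The cross-reference points to the whole list without exception, no selection rule is given, and a rule based on association with the outcome would be likely to pick this variable first. Nor does a near-copy announce itself as a perfect fit does.

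It can also be said that the two fentanyl variables may differ. The figure showing standard anaesthetic management is not available to this review, so routine postoperative fentanyl outside rescue use cannot be ruled out. The text describes none. If there were some, the covariate would still contain the outcome as a component, and the shrinkage would be smaller.

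**Conclusion.** The point holds as a wrongly fixed cross-reference. If followed to the full list, it makes the adjusted fentanyl analysis unable to do what it is for. The treatment effect is exactly zero if covariate and outcome are identical, and strongly shrunk if they are very highly correlated. Severity is minor to moderate, because the fault is confined to a sensitivity analysis of one secondary outcome. The t test or non-parametric test of fentanyl requirement, the primary outcome and the sample size are untouched.

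Three stronger readings are not supported:

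- **Any high correlation drives the effect to almost nothing.** Under the assumptions above, that is so only at about 0.97 or higher. A fifth of the effect remains at 0.90 and half at 0.72.
- **Rescue fentanyl is the trial's main check on lost analgesia.** The article does not rank it so. Pain has two planned analyses, and satisfaction with analgesia is tested as well.
- **Everything measured after randomisation must leave this model.** Randomisation is on the morning of surgery, so duration of surgery and intraoperative fentanyl also arise after it. They are nevertheless settled before the infusion starts and cannot be changed by it.

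The exact zero rests on algebra alone. The sizes in between rest on the assumed σ and s, and on the extra component U being independent of treatment and of rescue dose.

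**What to change.** **Necessary.** Add one sentence to Secondary outcome analysis stating that postoperative fentanyl dose is excluded from the covariates when supplemental fentanyl is the outcome.

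**Preferable.** Limit this model to variables fixed before the study infusion starts: age, BMI, duration of surgery and intraoperative fentanyl dose. This also drops duration of infusion and time to end of study, neither of which is settled when the infusion begins.

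The change should be made before database lock. It costs a line of wording and has no effect on sample size, data collection or any other planned test.
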